### 13.2.1 BI-participants

To test if data is normally distributed, residual plots and the Kolmogorov-Smirnov test will be used (SPSS 20.0, Chicago, IL, USA; MedCalc Software: version 12.07.0.0; Mariakerke, Belgium). In case of non-normal data distribution, primarily a logarithmic transformation is tried or secondarily a Box-Cox transformation will be attempted for normalization of data.

The differences calculated are:

$$\Delta\text{SHA}_{\text{high-sensitizers}} = \text{SHA}_{\text{NX high-sensitizers}} - \text{SHA}_{\text{PL high-sensitizers}} \text{ (max. values during one of the 3 TCI-steps)}$$

$$\Delta\text{SHA}_{\text{low-sensitizers}} = \text{SHA}_{\text{NX low-sensitizers}} - \text{SHA}_{\text{PL low-sensitizers}} \text{ (max. values during one of the 3 TCI-steps)}$$

$$\Delta\text{SHA}_{\text{sensitizers}} = \Delta\text{SHA}_{\text{high-sensitizers}} - \Delta\text{SHA}_{\text{low-sensitizers}}$$

A mixed model with random effect for subject and fixed-effects for the factors: *secondary hyperalgesia areas* (SHA); *sensitizers* (high-sensitizers/low-sensitizers); *target-controlled-infusion* (step 1/step 2/step 3); *HADS-scores*; and *PCS-scores*, are used for the primary outcome  $\Delta\text{SHA}_{\text{sensitizers}}$ . Non-significant ( $P > 0.05$ ) factors, beginning with interactions, are excluded until all included factors attain significance. Main-effects and interaction-effects are examined.

The risk of type I error is reduced by setting a significance level of 0.01 ( $\alpha$ ). A power of 0.90 ( $\beta = 0.10$ ) is set in order to reduce the risk of type II errors. For all statistical calculations, in which multiple comparisons are performed, Duncan's new multiple range test or Scheffé's method, as appropriate, will be used. Statistical calculations will be performed with partially un-blinded data, i.e., group A and B. When statistics have been completed data are unblinded into naloxone and placebo groups.

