## 2. AIM

The principal aims of the study are:

\* *first*, to investigate whether the administration of naloxone, a selective mu-opioid receptor (MOR) antagonist, can re-introduce clinical pain (at rest, during movement and in pressure-evoked condition) and hyperalgesia three to four weeks after a unilateral, mandibular third molar extraction procedure (TME).

\* *second*, to assess predictability of the latent sensitization response, assessed as naloxone-induced reinstatement of secondary hyperalgesia after resolution of an experimental burn-injury, according to individual sensitization phenotype (high-sensitizers vs. low-sensitizers).

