#### 3.1.2 Burn injury (BI) study

- Areas of secondary hyperalgesia assessed by a weighted-pin instrument (256 mN) 0, 1, 2 and 165-169 hrs (during TCI [time; 10-15"A; 44-49"; and 70-75"]) after the BI.

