#### 9.1.2.2 Burn injury days: Day 1 (right leg)/Day 3 (left leg; [Figs. 3 and 4]):

- The participants have been instructed to use a hair trimmer in the test areas on both lower legs, two days before each study session.
- It is verified that the participant belongs to either the low-sensitizer group or the high-sensitizer group.
- Urine-sample to test for opioids (sample is discarded just after the analysis).
- **Baseline assessments**, as previously described (Day 0; Fig. 4).

- **Burn injury induction**, as previously described (Day 0; Fig. 4).
  - **Post-injury assessments**, as previously described (Day 0; Fig. 4). However, an additional 2 hrs post-injury assessment is made at **time 2 hrs 7"** after induction of the burn injury (cf. 9.2.5.2), using a **green** marker.

[figure not shown]

**Fig 3.** General study layout for the burn injury (BI) study. BIs are induced Day 0, Day 1 and Day 3. Day 0 is a screening day, including high-sensitizers (large secondary hyperalgesia areas; 75% quartile) and low-sensitizers (small secondary hyperalgesia areas 25% quartile). Day 1 and Day 3 include induction of BIs in high- and low-sensitizers. Target-controlled-infusion (TCI) days are Day 2 and Day 4, with randomized allocation between placebo and naloxone. The time line between Day 1 and Day 2, and, Day 3 and Day 4, is 7 days. The timeline between Day 3 and Day 0 is 8 weeks or more.

[figure not shown]

**Fig 4.** Study layout for the burn injury (BI) study. Day 1/Day 3 includes induction of BI (mild thermal injury; 47C°, 7") with baseline assessments (green rectangle), burn injury (red) and post-injury assessments (blue). Day 2/Day 4 include a pre-drug assessment (blue; post-injury 165 hrs), drug-infusions (naloxone or placebo; 167-168 hrs) and assessments during target-controlled-infusion ([TCI]; light green). The estimated plasma concentrations are superimposed in dashed red line. Roman numerals indicate the three TCI-steps. Stars indicate assessments of pin-prick pain thresholds (red), and secondary hyperalgesia areas (green star).

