## **10.2 Blinding procedure, packing and labeling**

### **10.2.1 TME-participants and BI-participants**

This is a cross-over, block-randomized, double-blind study. Randomization (computer generated using Randomization.com; sequence-randomization in blocks of four subjects), and, manufacturing, packaging and labelling of drugs will be performed by Skanderborg Hospital Pharmacy (att. Pharmacist [name]). Two sets of non-transparent sealed envelopes with the complete randomization list will be prepared. These contain information on which treatment each participant participating in the study will receive. The sponsor stores one of the envelopes, while the other one is kept by the investigator at the Department of Anesthesiology HOC, 4231 Rigshospitalet in a secure locked place. The Skanderborg Hospital Pharmacy keeps the un-blinded randomization list, which will be sent to the investigator for data analysis after the study is finished. Individual drug-packages, for each participant, containing two 100 ml ampoules of normal saline and naloxone 4 mg/ml, respectively, include a sealed, non-transparent envelope containing the randomization sequence code, to be broken in case of a medical emergency (paragraph 12.4, page 29).

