### 13. STATISTICAL ANALYSES

#### 13.1 Sample size calculations

##### 13.1.1 TME-participants

Sample size calculations are based on following assumptions and estimations (abbreviations: BL = baseline; NX = naloxone; PL = placebo; TCI = during target-controlled-infusion):

1. a primary outcome based on a summed measure (SM) of resting pain (RP), masticatory pain (MP; (movement-related) and pressure-evoked pain (PM; pressure algometry [100 kPa]).  $NRS_{SM} = NRS_{RP} + NRS_{MP} + NRS_{PM}$ .
2. the summed pain intensities (SPIs) are calculated as: (BL-SPINX) and (TCI-SPINX), and, (BL-SPIPL) and (TCI-SPIPL), where (TCI-SPI) indicates SM-value at highest obtainable TCI-step (Fig. 2).
3. the summed pain intensity differences (SPIDs) are the differences: **SPIDNX** = (TCI-SPINX) – (BL-SPINX) and **SPIDPL** = (TCI-SPIPL) - (BL-SPIPL)

4. the mean [SD] BL-pain intensities are estimated to be: resting pain 1 [1] NRS-units; movement related pain 2 [2] NRS-units; pressure evoked pain 4 [2] NRS-units.
5. the mean [SD] summed BL-pain intensity (BL-SPI) is estimated to be 7 [4.1] NRS-units (Table 2).
6. the minimal relevant SPID-difference, calculated as  $\Delta SPID = SPID_{NX} - SPID_{PL}$  is estimated to be 5 (NX-group: RP = 4; MP = 5; PM = 7 [total 16]/PL-group: RP = 2; MP = 4; PM = 5 [total 11]) corresponding to a  $\Delta SPID\% = 45\%$ .
7. the design is a placebo-controlled, randomized, double-blind, crossover study
8. the significance level  $\alpha$  is set to 0.01 and the power is set to  $= 0.90$  ( $\beta = 0.10$ )

The total number of individuals estimated to be included in the study is calculatedE to be 14 (effect size 1.2). Using the range of variances in Table 2, it can be calculated that the number of individuals ranges from 9 to 19, with effect sizes of 1.7 to 1.0, respectively.

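### The burn-injury primary contrast does not use the same-day pre-infusion (165 h) hyperalgesia area, and the one model term that might be that baseline is undefined and removable

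*Protocol*

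**What the plan says.** The second aim (section 2) concerns "naloxone-induced reinstatement of secondary hyperalgesia after resolution of an experimental burn-injury", compared between high- and low-sensitizers.

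The Fig. 4 legend in section 9.1.2.2 shows that the area is mapped before the drug on both infusion days: "Day 2/Day 4 include a pre-drug assessment (blue; post-injury 165 hrs". Section 9.1.2.3 calls this mapping a baseline and starts the infusion at 167 h 20 min. Days 1 and 2 use the right leg and Days 3 and 4 the left. The left leg is also the one tested at screening on Day 0.

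The primary outcome (section 3.1.2) is "Areas of secondary hyperalgesia assessed by a weighted-pin instrument (256 mN) 0, 1, 2 and 165-169 hrs". A bracket limits the last interval to three windows during infusion.

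Section 13.2.1 (BI-participants) computes, in each sensitizer group, the naloxone area minus the placebo area, using "max. values during one of the 3 TCI-steps", and then the difference between the groups. The mixed model has "fixed-effects for the factors: *secondary hyperalgesia areas* (SHA); *sensitizers* (high-sensitizers/low-sensitizers"), followed by infusion step, HADS and PCS. It is then reduced: "Non-significant ( $P > 0.05$ ) factors, beginning with interactions, are excluded until all included factors attain significance".

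In the third-molar study, section 13.1.1 subtracts the same-session baseline: "the summed pain intensity differences (SPIDs) are the differences" between the value during infusion and the value at baseline.

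**The concern.** The question is whether hyperalgesia returns after it has resolved. No section requires the area to have resolved at 165 h, and the response as defined does not show whether it had. The measurement that would show it is collected in both sessions and has no stated place in the primary analysis.

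Each session follows its own burn on its own leg, so one participant's residual area can differ between the two days. That difference goes straight into his naloxone-minus-placebo value. The aim is to relate individual response to phenotype, so noise at the individual level matters. Leg is also fully confounded with period, and the listed factors include no period term.

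**Working it through.** **Inputs.** Section 13.1.2 gives the planning data, n = 3 per group, as mean (SD) in cm² at 168 h:

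| Group | Placebo | Naloxone | Difference in means |
|---|---|---|---|
| High-sensitizers | 2.1 (2.5) | 111.0 (26.3) | 108.9 |
| Low-sensitizers | 0.3 (0.1) | 0.9 (0.6) | 0.6 |

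The planned size is 20 + 20, with alpha 0.01 and power 0.90. The protocol gives neither the SD of the 165 h area nor its correlation with the area during infusion.

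**The plan's own figures.** With a two-sided alpha, the stated sizes of 5 and 18 reproduce.
- High: 108.9/√(26.3² + 2.5²) = 4.12, and a paired t-test needs 5.
- Low: the stated effect size of 1.4 is 0.6/√((0.6² + 0.1²)/2) = 1.395, an independent-groups quantity that gives 18 per group. A paired calculation from the same SDs with zero within-subject correlation gives 0.6/√(0.6² + 0.1²) = 0.99 and needs 19.

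**Does residual area bias the mean contrast?** A simulation with no drug effect, n = 20, assumed measurement SD of 2 cm² and assumed between-session SD of residual/2 + 1 gave:

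| Mean residual in both sessions (cm²) | Mean naloxone − placebo | Naloxone session alone |
|---|---|---|
| 0 | −0.01 | 2.1 |
| 2.1 | 0.00 | 4.0 |
| 10 | 0.05 | 11.9 |
| 20 | −0.06 | 21.8 |

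The naloxone session alone would mislead; the contrast does not.

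**When can residual area enter a group mean?** Randomisation is "sequence-randomization in blocks of four subjects" (section 10.2.1), and no stratification by sensitizer group is stated. Suppose 12 of 20 in a group receive naloxone on one leg and 8 on the other. Then (12 − 8)/20 = 0.2 of the left–right difference in residual area enters that group's mean. As an illustration, take that difference to be as large as the whole planning placebo area:
- High: 0.2 × 2.1 = 0.42 cm², against an effect of 108.9.
- Low: 0.2 × 0.3 = 0.06 cm², against an effect of 0.6, or 10%.

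**Precision on the planning SDs.** Assume the residual SD on each day equals the placebo SD at 168 h, that the days are independent, and that the residual adds to the infusion area.
- High: 2 × 2.5² = 12.5, out of 26.3² + 2.5² = 697.9. The share is 1.8%, so ρ ≈ 0.13. The SD falls by 1 − √(1 − 0.018) = 0.9%, and 20/(1 − 0.018) ≈ 20.4 equivalent subjects.
- Low: 2 × 0.1² = 0.02, out of 0.6² + 0.1² = 0.37. The share is 5.4%, so ρ ≈ 0.23. The SD falls by 2.7%, and 20/(1 − 0.054) ≈ 21.1 equivalent subjects.

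**Precision over an assumed range.** Let ρ be the correlation between the 165 h difference and the infusion difference. Covariate adjustment multiplies the variance by 1 − ρ². With equal SDs, subtraction multiplies it by 2(1 − ρ).

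| ρ (assumed) | Covariate: variance factor | SD cut | Equivalent n, 20/(1 − ρ²) | Subtraction: variance factor |
|---|---|---|---|---|
| 0.3 | 0.91 | 5% | 22 | 1.4 |
| 0.5 | 0.75 | 13% | 27 | 1.0 |
| 0.7 | 0.51 | 29% | 39 | 0.6 |

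Subtraction therefore loses precision below ρ = 0.5 when the SDs are equal. In general it loses when ρ is below half the ratio of the baseline-difference SD to the infusion-difference SD.

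**The case against.** A reader might infer that an area which never resolved is scored as reinstatement. The documents do not support that. Every naloxone value is set against the same participant's placebo session, in randomised order, so residual area present on both days cancels. The distortion is confined to participants whose residual differs between days.

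A reader might also infer that the plan ignores the baseline altogether. That is too strong, because the SHA factor could be meant as the 165 h area. The protocol does not say so, however, and the reduction rule can remove the factor.

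The comparison with the third-molar study is only partly fair. There the expected summed baseline is 7 (SD 4.1) NRS units. Section 4.2.2.1 expects burn signs to subside in most cases within 24 to 48 h, and the planning placebo areas at 168 h are close to zero. Different handling can be defended, although no reason is given. The Day 0 burn precedes Day 3 by at least 8 weeks (Fig. 3 legend), so its influence on the left leg is a possibility only.

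The strongest objection concerns size. The planning SDs imply correlations of about 0.13 and 0.23, below the whole assumed range of 0.3 to 0.7. In a two-group comparison of 40, the covariate uses one of 38 residual degrees of freedom (2.6%), which is of the same order as the 1.8% and 5.4% variance shares. This objection stands, except that it rests on three subjects per group, which the protocol itself calls extremely few.

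Finally, covariate details are often left to an SAP, and one may exist that defines the factor. Here, though, the protocol itself writes out the contrast, the factor list and the elimination rule, so the gap lies in stated text.

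**Conclusion.** The point holds in a limited form. The stated primary contrast omits a same-day baseline that is already collected, and the only term that could supply it is undefined and removable. The mean contrast is unbiased in expectation. What remains is session-to-session residual variation in the individual differences and their error term, plus a possible shift in a group mean of 0.2 times the left–right residual difference under a 12/8 sequence split.

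The expected precision gain is small on the planning data: about 1% of the SD in high-sensitizers and 3% in low-sensitizers, under the additive assumption. It reaches 5%, 13% or 29% only if the true correlation is 0.3, 0.5 or 0.7, which would need residual areas that are larger or more closely related to the infusion areas than the planning data suggest. The case for the change therefore rests mainly on a definite analysis that matches the aim, and on protection if residuals prove larger than planned.

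**What to change.** In section 13.2.1 (BI-participants), state that the 165 h secondary hyperalgesia area is a fixed covariate in the primary model and is exempt from backward elimination. Use the naloxone-day minus placebo-day difference if the response is the participant's difference, or the session's own 165 h value if sessions are modelled separately. Define the SHA factor accordingly.

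Do not replace the response with simple change from 165 h. Where the correlation is low that adds variance, while a covariate lets the data set the slope.

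The cost is one line of text and one degree of freedom. No new measurement is needed.

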### 13.1.2 BI-participants

Data from our previous high-dose naloxone study (Pereira MP et al [2015] PLOS One 10: e0134441. 10.1371/journal.pone.0134441 [doi]) indicate:

1. for the high-sensitizers ( $n = 3$ ): secondary hyperalgesia areas 168 hrs after the BI during placebo infusion, mean (SD),  $2.1 \text{ cm}^2$  ( $2.5 \text{ cm}^2$ ) and during naloxone infusion  $111.0 \text{ cm}^2$  ( $26.3 \text{ cm}^2$ ).
2. for the low-sensitizers ( $n = 3$ ): secondary hyperalgesia areas 168 hrs after the BI during placebo infusion,  $0.3 \text{ cm}^2$  ( $0.1 \text{ cm}^2$ ) and during naloxone infusion  $0.9 \text{ cm}^2$  ( $0.6 \text{ cm}^2$ ).

Using the significance level  $\alpha$  set to 0.01 and the power set to  $= 0.90$  ( $\beta = 0.10$ ), the estimated number of individuals needed to reject the null hypothesis in the high-sensitizers are 5 (effect size 4.1; sic!) and in the low-sensitizers are 18 (effect size 1.4). Since the data used for sample size estimates are made on an extremely limited number of individuals, and, since the study of nature is a proof-of-concept, it was decided to include 20 high-sensitizers and 20 low-sensitizers. Boot-strapping techniques could have been used, but we considered the number individuals used in the sample estimate too extreme. On the other hand, if a larger number of subjects are needed, the clinical significance is deemed of dubious value.

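### The burn-injury primary model cannot be fitted as written: its outcome is a between-group contrast that no participant has, and the elimination rule can remove the term that tests aim 2

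*Protocol*

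**What the plan says.** Protocol section 13.2, BI-participants, defines a naloxone-minus-placebo difference in secondary hyperalgesia area for the high-sensitizers and another for the low-sensitizers. Each uses the maximum over the three infusion steps. It then defines ΔSHA_sensitizers as the first minus the second and makes this the primary outcome of "A mixed model with random effect for subject and fixed-effects for the factors" SHA, sensitizers (high/low), infusion step (1/2/3), HADS and PCS.

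Two further rules apply to this model:
- Terms with P>0.05 are dropped: "factors, beginning with interactions, are excluded until all included factors attain significance". No term is exempt.
- If data are non-normal, "primarily a logarithmic transformation is tried or secondarily a Box-Cox transformation will be attempted for normalization of data". No offset is given. Unlike the third-molar (TME) part of 13.2, no rank-based alternative is named.

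Sections 7.1.2 and 9.1.2 place each continuing participant in exactly one group by screening area (at least 37 cm² or at most 22 cm²). Section 13.1.2 takes its planning values, "secondary hyperalgesia areas 168 hrs after the BI during placebo infusion" and during naloxone, from 3 earlier subjects per group, and plans 20 per group at α = 0.01.

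**The concern.** This model is the protocol's stated test of its second aim: whether sensitization phenotype predicts reinstatement of hyperalgesia after naloxone. If the outcome does not exist at participant level, whoever runs the analysis must invent a replacement, possibly after seeing the data. The elimination rule adds a second risk. If the sensitizer term has P>0.05 it leaves the model, and the trial then reports no estimate for the question it was built to answer. The transformation rule matters because participants with no reinstated hyperalgesia, who are central to a predictability question, are the ones most likely to have values that cannot be logged.

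**Working it through.** **1. Outcome against factors (13.2, BI-participants)**
- Outcome: mean difference in high-sensitizers minus mean difference in low-sensitizers. This is one number for the whole trial. A random subject effect needs at least one value per participant, and there is none.
- Sensitizer group: already subtracted out of the outcome.
- Infusion step: already collapsed by taking the maximum over steps.
- SHA: listed as a predictor without saying which measurement. Areas are taken at 0, 1 and 2 h after the burn, at 165 h before infusion, and during infusion (3.1.2, 9.1.2). The infusion-period areas make up the outcome itself.
- Drug: not listed, so the text cannot be rescued by reading it as a model for raw SHA with a drug-by-group term.

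**2. The plan's own sample-size figures (13.1.2; α = 0.01 taken as two-sided, power 0.90)**
- High: difference 111.0 − 2.1 = 108.9 cm². SD of the difference at zero within-subject correlation = √(26.3² + 2.5²) = 26.42. Effect size 108.9/26.42 = 4.12, and a paired t-test needs n = 5. This matches the stated 4.1 and 5.
- Low: difference 0.9 − 0.3 = 0.6 cm². The stated 1.4 is 0.6/√((0.6² + 0.1²)/2) = 0.6/0.430 = 1.395, and a two-sample t-test needs 18 per group. This matches the stated 18. The paired version at zero correlation is 0.6/√(0.6² + 0.1²) = 0.6/0.608 = 0.99, n = 19.
- So the two figures come from different test families. The planned 20 per group still covers 19.

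**3. How unequal the spreads are**
- Naloxone: 26.3/0.6 = 43.8. Placebo: 2.5/0.1 = 25. Difference: 26.42/0.608 ≈ 43.
- With n = 3 per group, the normal-theory 95% interval for the 43.8 ratio is about 7 to 274. The size is very uncertain; the direction is not.

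**4. Effect on high v low (one difference per participant, α = 0.01)**

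Because the low-group SD is negligible next to the high-group SD, the pooled test rejects when |t| on n_H − 1 df exceeds 2.712 × √[ (n_H − 1)/38 × (1/n_H + 1/n_L) × n_H ].
- 20 v 20: multiplier 1.000, P(|t₁₉| > 2.712) = 0.0138. Simulation (100,000 runs, SDs 26.6 and 0.43 implied by the stated effect sizes): 0.0135 pooled, 0.0098 Welch.
- 15 high/25 low: multiplier 0.768, P(|t₁₄| > 2.082) = 0.056 pooled. Welch simulated 0.0103.
- 25 high/15 low: multiplier 1.298, P(|t₂₄| > 3.519) = 0.0018 pooled. Welch simulated 0.0097.
- Welch df at 20 v 20 ≈ 19, against 38 pooled.

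**5. Within-group naloxone v placebo, if a pooled SD were used**
- Pooled SD = √((26.42² + 0.608²)/2) = 18.69.
- High: P(|t₁₉| > 2.712/√2 = 1.917) = 0.070 at nominal 0.01.
- Low: 0.6/(18.69/√20) = 0.14 standard errors, so power is about 1% or less. With the group's own SD of 0.608 it is 92.5%.

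**6. Values that log or standard Box-Cox cannot take**
- P(low-group difference ≤ 0), normal approximation: Φ(−0.6/0.43) = 8%; Φ(−0.6/0.608) = 16%. That is 1.6 to 3.2 of 20, with an 82-97% chance of at least one.
- Raw areas can also be 0: section 9.2.5.2 says uninjured skin normally has no such area.

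**The case against.** The strongest defence is that this is a drafting fault with an obvious repair. The two group differences and their contrast are all computable, so a reader might infer that aim 2 cannot be tested at all, and that would go too far. This defence stands, but it does not save the model as specified. Several stronger readings are also unsupported:

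- **That the plan pools the variances.** The section states neither a common nor a group-specific variance, and an unseen SAP may settle it.
- **That the primary test has a 7% type I error.** The 7% in high-sensitizers and the near-zero power in low-sensitizers concern within-group contrasts. Section 13.1.2 sizes the groups on these, but 13.2 does not name them as primary. For high v low at the planned 20 v 20, pooling costs about 0.004.
- **That omitting drug is an error in itself.** A naloxone-minus-placebo outcome already contains drug.
- **That SHA is circular.** A pre-infusion SHA would be a legitimate covariate. The fault is that the text does not say which SHA.
- **That differences will be logged and non-responders lost.** The text says only that data are transformed, and an offset could be specified. Nor does the 4-of-12 response in section 1.1 show that the other eight had non-positive differences. What stands is that the rule as written fails for zero areas and for non-positive differences alike.
- **That elimination could discard a significant result.** A term removed at P>0.05 has already missed 0.01 at that step. The loss is the estimate and interval, plus data-driven covariate choice.

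**Conclusion.** The point holds for the specification of the model. The stated outcome has no participant-level values, two listed factors are consumed in its construction, one predictor is unidentified, and the key term is not protected from elimination. None of this rests on planning figures or on anything a SAP would merely fill in: the protocol names the outcome and the factors, and they are incompatible.

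The variance point is supporting. It rests on 3 subjects per group, normality and, for the difference SDs, an assumed within-subject correlation. On those figures, not assuming a common variance changes the primary type I error from about 0.014 to 0.010 at 20 v 20, and from 0.056 to 0.010 at 15 high/25 low. The transformation point rests on zero areas being possible and on an 8-16% share of non-positive low-group differences under a normal approximation.

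**What to change.** In section 13.2, BI-participants:

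1. Define one ΔSHA per participant: maximum over the three steps on naloxone minus maximum over the three steps on placebo.
2. Make the primary test high v low sensitizers by Welch t-test at α = 0.01, and report the difference with its confidence interval whatever the P value. An ordinary permutation test of the mean difference is not a substitute, because its simulated type I error is about 0.013, close to the pooled test.
3. Drop the elimination rule, or exempt the sensitizer term from it.
4. Remove SHA as a predictor, or name a specific pre-infusion SHA as covariate.
5. If a step-wise mixed model is kept, use SHA at each step as outcome, with drug, group, drug×group, step and period, a random subject effect and group-specific residual variances.
6. Replace log/Box-Cox with a method valid for zero and negative values.
7. Base any within-group naloxone-placebo test on that group's own variance.

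This is a change of wording only, with no new data or visits. The statistical cost is about 19 degrees of freedom for Welch instead of 38.
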